### Primary and secondary outcomes

The primary outcome of this study is the days per week of corticosteroid use, compared between the Staphefekt and the placebo group over 12 weeks. Patients report their triamcinolone use daily in a secured digital platform, “DermHome”.^1^ Additionally, the use of triamcinolone cream will be measured in grams by weighing the study medication at the time of issue and return (each visit). Secondary outcomes include clinical efficacy and QoL from baseline through week 12 and week 20, change in the microbial composition (including *S. aureus)* and safety. Clinical efficacy is measured using the EASI, the Investigator’s Global Assessment (IGA) and registration of the number of flares [28]. A flare is defined as an exacerbation that requires the need to intensify treatment, from a doctor or patient’s perspective. This implies stronger topical therapy or the need for systemic treatment. A 50% increase in the EASI score compared to baseline is used as an indication to intensify treatment. The Pruritus Numerical Rating Scale (Pruritus NRS) and the Patient Orientated Eczema Measure (POEM) are included as patient-reported efficacy outcomes [29, 30]. QoL is measured using the Skindex-29 [31, 32]. Changes in the microbiome are evaluated by comparing the changes in bacterial composition between the treatment groups, determined by 16S rRNA sequencing of the skin scrub samples. Reduction in *S. aureus* is determined by quantitative PCR (and culture for the comparison between visit 2a and visit 2b). Safety and tolerability is assessed by monitoring the incidence of (serious) adverse device events through the end of the study, evaluated by medical check-ups that include evaluation of vital signs. Reportable adverse events will be reported within the set timelines to the competent authorities. Table 2 gives a detailed overview of the measurements per visit.^1^

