**Methods:**

This is a multi-centre, placebo-controlled, double-blinded and randomized superiority trial with a parallel group design. A total of 100 participants, aged 18 years or older, diagnosed with moderate to severe AD and using a topical corticosteroid in the weeks before enrolment are included in the study. The study is executed in the Erasmus MC University Medical Centre Rotterdam in collaboration with the Havenziekenhuis Rotterdam. After a 2-week run-in period to standardize the corticosteroid use with triamcinolone acetonide 0.1% cream, participants will be randomized to either treatment with Staphefekt in a cetomacrogol-based cream or a placebo for 12 weeks, followed by an 8-week follow-up period. The primary objective is to assess the difference in the need for corticosteroid co-therapy between the Staphefekt and the placebo group, measuring the number of days per week of corticosteroid cream (triamcinolone) use. Secondary outcomes include the difference in use of corticosteroid cream measured in grams, differences in clinical efficacy, quality of life (QoL), microbial composition (includi23ng *S. aureus*) between the Staphefekt and the placebo group, and the safety and tolerability.

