## Methods/design

### Design and setting

The MAAS trial (Microbiome in atopic dermatitis during anti-staphylococcal therapy and the effect on steroid use), is a multi-centre, randomized, double-blinded, placebo-controlled superiority trial with a parallel group design (Fig. 1). The study aims to evaluate the effect of Staphefekt on the use of corticosteroids, disease severity, QoL and composition of the microbiome in patients with AD. The study was designed by the Department of Dermatology of the Erasmus MC University Medical Centre Rotterdam and will be executed in collaboration with the Havenziekenhuis Rotterdam. Enrolment and follow-up visits take place at these two locations. Participants who comply with the criteria for inclusion and exclusion will start with a 2-week run-in period to standardize the corticosteroid use with triamcinolone acetonide 0.1% cream. After completion of the run-in phase, participants will be randomized to either treatment with Staphefekt or a placebo for 12 weeks, followed by an 8-week follow-up period. An Eczema Area Severity Index (EASI) above 50 after the run-in phase is a contraindication for further participation. During the course of the study, participants visit the outpatient clinic six times (visit 1 through 6) and data will be collected on corticosteroid use, disease severity, QoL, skin microbiome and adverse events. See Additional file 1 for an overview of the Standard Protocol Items: Recommendations for Interventional Trials (SPIRIT) 2013 checklist items. See Table 2 for the SPIRIT diagram of the trial procedures.

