## Discussion

The MAAS trial is a randomized, placebo-controlled trial that investigates the effect of 3-month anti-staphylococcal therapy with Staphefekt on topical corticosteroid use, clinical symptoms and QoL in adults with moderate to severe AD. Additionally, data will be collected about the growth characteristics of the skin microbiome, including *S. aureus*. Taking into consideration the current literature on anti-staphylococcal therapy, a study design using a long-term anti-staphylococcal intervention, measuring long-term outcomes was chosen.

Evidence for the clinical efficacy of Staphefekt, registered as a class 1 medical device in Europe, is based on in vitro studies and a case series [18–20]. These in vitro studies showed that Staphefekt kills different strains of *S. aureus* (also methicillin-resistant strains), without harming the commensal flora or inducing bacterial resistance [19]. A case series describes clinical improvement in *S. aureus* related symptoms, such as folliculitis and superinfected dermatitis, and no development of resistance during long-term daily treatment with Staphefekt based on the minimal inhibitory concentrations of the cultured *S. aureus* strains over time [35]. The lack of resistance induction can be expected, as bacterial killing by an endolysin is independent of the involvement of the bacterial metabolism. The co-evolution of bacteriophages and their host bacteria over millions of years, ensures that phage endolysins attack essential bonds in the bacterial cell wall that cannot be adapted by the host [22]. Thereby, the lytic activity of exogenously applied endolysins results in lysis of the target cells within seconds, restricting the possibility to adapt and develop resistance. Furthermore, attacking several bonds of the bacterial wall simultaneously by the use of more than one enzymatically active domain in the Staphefekt molecule, makes resistance even less likely to develop [18].

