Because of the proteinaceous nature of endolysins, immunogenicity can be of concern. The literature shows the possibility of the formation of non-neutralizing antibodies against lysins other than Staphefekt [22]. In a study in which the presence of anti-Staphefekt IgG was evaluated in serum from 21 Staphefekt-naive healthy human donors, pre-existent IgG antibodies recognizing Staphefekt epitopes were detected in all the donors (unpublished data). This can be explained, as humans are exposed daily to *S. aureus* and therefore to bacteriophages and their lysins. However, Staphefekt is a large protein molecule (>50 kDa), making penetration through the skin and mucosa and subsequent antibody reactions unlikely [36].

Calculation of the sample size for this study was hampered as no information was available about the effect of Staphefekt on corticosteroid use and clinical efficacy in AD. Therefore, the study should be considered as hypothesis generating, giving insight into effect sizes and distributions of clinical outcomes. Our expected effect size was based on a study of Hon et al. of the effect of bleach on corticosteroid use in AD. We chose a slightly higher effect size, because we expect the effect of Staphefekt that specifically targets *S. aureus* to be more efficacious than bleach. We consider this effect size, a reduction in corticosteroid use of more than 1 day a week over 12 weeks, as clinically relevant because of the (low) risk of side effects and a general reluctance of patients to use corticosteroids, resulting in poor compliance and a lack of treatment efficacy [37, 38].

No consensus has been reached yet on a standardized outcome for long-term AD control, the primary goal of our study. The Harmonising Outcome Measures for Eczema (HOME) initiative reached consensus on the use of EASI and POEM as doctor-based and patient-based measures of AD severity, both of which are included as secondary outcomes in this trial [39]. According to the authors of HOME, measures of long-term control could include time to flare and the use of rescue medicine [39]. Next to corticosteroid use, both these study outcomes were included in this study as secondary parameters.

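### The safety outcome is defined by adverse device events, which on its ordinary reading is narrower than the adverse events the trial collects; the two statements should be reconciled

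*Protocol article*

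**What the plan says.** The protocol article describes safety in several places, and the terms differ.

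- **Abstract, Methods:** the secondary outcomes end with "and the safety and tolerability". No limit to the device is given.
- **Design and setting:** over the six visits, "data will be collected on corticosteroid use, disease severity, QoL, skin microbiome and adverse events". Again there is no device limit, but the word all is not used either.
- **Primary and secondary outcomes:** this section defines the outcome. Safety is judged through "monitoring the incidence of (serious) adverse device events through the end of the study". Events are picked up at clinical examinations, with vital signs among the checks. The next sentence returns to the broader term, for regulatory purposes only: "Reportable adverse events will be reported within the set timelines to the competent authorities".
- **Discussion:** the product is "registered as a class 1 medical device in Europe", which explains where the device vocabulary comes from. The same section describes the target reduction in corticosteroid use "as clinically relevant because of the (low) risk of side effects and a general reluctance of patients to use corticosteroids".

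The article does not define an adverse device event, name who judges relatedness, or give a rule for that judgement.

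**The concern.** In ordinary use, an adverse device event is an adverse event judged to be related to the device. If that is the meaning here, the safety outcome passes through a causality judgement before the arms are compared. A randomised, placebo-controlled design makes that step unnecessary, because any excess of events in one arm can be read directly from the comparison by arm.

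The step matters more than usual for this product. The Sample size section calls this the first study of its clinical outcomes in atopic dermatitis, and the Discussion rests the existing evidence on laboratory work and a case series. An investigator therefore has little experience on which to decide which events the product could cause. The Discussion also regards antibody reactions as unlikely, an expectation that could lower the chance that such an event is attributed.

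A second consequence concerns the other treatments. Triamcinolone is used throughout and escape medication is permitted (Intervention). On the ordinary reading, events due to either would fall outside the stated safety outcome.

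**Working it through.** No figure in the article bears on the safety outcome. The only calculated figure, 40 per arm raised to 50, is for days of corticosteroid use. The check is therefore a comparison of wording, followed by a short argument about what an attribution filter does.

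**Step 1: what is collected against what is counted.**

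| Place | Term used | Purpose |
|---|---|---|
| Abstract, Methods | safety and tolerability | secondary outcome |
| Design and setting | adverse events | data collected at visits |
| Primary and secondary outcomes | (serious) adverse device events | definition of the safety outcome |
| Primary and secondary outcomes, next sentence | reportable adverse events | reporting to authorities |

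The narrowest term stands in the one place that defines the outcome. The section on data analysis applies mixed models to the secondary outcomes and gives safety no separate definition, so nothing later widens it. No comparison by arm of adverse events regardless of relatedness is stated.

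**Step 2: what the filter does.** Suppose a proportion *b* of patients in each arm has a background event and the product adds an excess *d* in the active arm. Let *f0* be the share of background events attributed to the device and *f1* the share of excess events so attributed. As a simple additive approximation:

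- all events: difference = (*b* + *d*) − *b* = *d*
- device events: difference = (*f0·b* + *f1·d*) − *f0·b* = *f1·d*

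The background terms cancel because blinding (Randomization and blinding) gives no reason for *f0* to differ between arms. Two cases follow.

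- If the harm is unsuspected, *f1* is near 0 and the device-event count shows almost nothing, whatever the size of *d*.
- If the harm is readily recognised, *f1* is near 1. The count keeps the difference and drops background events, so it can be the sharper comparison.

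The article gives none of *b*, *d*, *f0* or *f1*. Neither the size nor the direction of the effect on power can be stated.

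**Step 3: corticosteroid and escape-medication events.** These have a cause other than the device. On the ordinary reading they contribute nothing to the count, whichever arm they fall in.

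**The case against.** The strongest reply is that the term is loose wording in a trial of a registered device. The sentence excludes nothing explicitly, the check-ups and vital signs it relies on are not specific to the device, and the next sentence speaks of adverse events. Event definitions, relatedness rules and safety tables are also commonly left to a full protocol or analysis plan, neither of which is shown, and the table of procedures is not legible here. This stands in part: the text does not establish that the sponsor intends to ignore unrelated events. It does not remove the point, because the article makes a positive statement of what the outcome is, and that statement does not match its own account of what is collected. If all adverse events were meant, the same correction is needed.

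Three stronger readings are tempting, and the documents do not support them.

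- **That all adverse events are collected and only device events are counted.** Neither all nor only is in the text.
- **That the safety comparison is biased by arm.** Participants and researchers are blinded, so relatedness would be judged without knowledge of treatment.
- **That the trial fails to test a claim of fewer corticosteroid side effects.** The Discussion cites their risk, which it calls low, together with patients' reluctance and poor compliance, as reasons why the target effect is relevant. No stated objective is to show fewer such effects.

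It is also fair to say that the trial is not powered for safety and calls itself hypothesis generating.

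**Conclusion.** The point holds as a mismatch of terms with a practical consequence. The defined safety outcome is, on its ordinary reading, narrower than the adverse events collected and than the secondary outcome given in the abstract. Followed as written, it could miss harms not attributed to a product with little clinical experience behind it, and it would not count events due to triamcinolone or escape medication.

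The conclusion rests on one assumption, that an adverse device event requires a relatedness judgement; the article does not define the term. The consequence is lost information, and its size cannot be taken from the document. A reader might infer a definite loss of power, but that depends on attribution shares the article does not give, and a well-recognised harm could show more clearly among device events. This favours reporting both counts. The change is a cheap improvement and does not touch the primary analysis.

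**What to change.** Reconcile the Design and setting section with the Primary and secondary outcomes section. Define the safety and tolerability outcome as the incidence of (serious) adverse events, regardless of relatedness, compared by randomised arm through the end of the study. Show device-related events as a subset, and triamcinolone-related events as another where that attribution is recorded. If the term adverse device event is kept for the subset, define it and say who makes the judgement.

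The cost is a changed sentence and one extra table, built largely from data that the article already says are collected. The downside is a longer listing with more background events; the device-related subset keeps the focused view available.

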### Data collection, monitoring and data analysis

Data collected during the visits are entered in Open Clinica. This data management system allows direct data entry. Data entry is monitored by an independent researcher according to a predefined monitoring plan. Triamcinolone use and itch scores filled in daily by the patients in “DermHome” will be extracted in an SPSS format and combined with the Open Clinica database. Patient confidentiality will be ensured by using identification numbers. Data will be analysed on an intention-to-treat basis. A mixed linear regression model will be used to examine if there is a significant difference in corticosteroid use over 12 weeks between the intervention and the placebo group [34]. This model accounts for repeated measurements in each patient and is valid in the case of missing data. Covariates that could influence the outcome variable will be included in the model. Subgroup analysis will be performed to analyse patients who are positive for *S. aureus* on the skin versus patients that are negative for *S. aureus* before the start of the intervention. Positive patients are defined as having positive cultures both at visit 1 and 2a. Negative patients must have two negative cultures. Patients that have one positive and one negative culture will not be included in the subgroup analysis. Secondary outcomes will also be analysed using a mixed model analysis (linear or logistic according to the type of data). The findings of this study will be published in national and international journals (according CONSORT 2010 Statement) and will be communicated to the relevant patient associations.

## Discussion

The MAAS trial is a randomized, placebo-controlled trial that investigates the effect of 3-month anti-staphylococcal therapy with Staphefekt on topical corticosteroid use, clinical symptoms and QoL in adults with moderate to severe AD. Additionally, data will be collected about the growth characteristics of the skin microbiome, including *S. aureus*. Taking into consideration the current literature on anti-staphylococcal therapy, a study design using a long-term anti-staphylococcal intervention, measuring long-term outcomes was chosen.

Evidence for the clinical efficacy of Staphefekt, registered as a class 1 medical device in Europe, is based on in vitro studies and a case series [18–20]. These in vitro studies showed that Staphefekt kills different strains of *S. aureus* (also methicillin-resistant strains), without harming the commensal flora or inducing bacterial resistance [19]. A case series describes clinical improvement in *S. aureus* related symptoms, such as folliculitis and superinfected dermatitis, and no development of resistance during long-term daily treatment with Staphefekt based on the minimal inhibitory concentrations of the cultured *S. aureus* strains over time [35]. The lack of resistance induction can be expected, as bacterial killing by an endolysin is independent of the involvement of the bacterial metabolism. The co-evolution of bacteriophages and their host bacteria over millions of years, ensures that phage endolysins attack essential bonds in the bacterial cell wall that cannot be adapted by the host [22]. Thereby, the lytic activity of exogenously applied endolysins results in lysis of the target cells within seconds, restricting the possibility to adapt and develop resistance. Furthermore, attacking several bonds of the bacterial wall simultaneously by the use of more than one enzymatically active domain in the Staphefekt molecule, makes resistance even less likely to develop [18].

Because of the proteinaceous nature of endolysins, immunogenicity can be of concern. The literature shows the possibility of the formation of non-neutralizing antibodies against lysins other than Staphefekt [22]. In a study in which the presence of anti-Staphefekt IgG was evaluated in serum from 21 Staphefekt-naive healthy human donors, pre-existent IgG antibodies recognizing Staphefekt epitopes were detected in all the donors (unpublished data). This can be explained, as humans are exposed daily to *S. aureus* and therefore to bacteriophages and their lysins. However, Staphefekt is a large protein molecule (>50 kDa), making penetration through the skin and mucosa and subsequent antibody reactions unlikely [36].

Calculation of the sample size for this study was hampered as no information was available about the effect of Staphefekt on corticosteroid use and clinical efficacy in AD. Therefore, the study should be considered as hypothesis generating, giving insight into effect sizes and distributions of clinical outcomes. Our expected effect size was based on a study of Hon et al. of the effect of bleach on corticosteroid use in AD. We chose a slightly higher effect size, because we expect the effect of Staphefekt that specifically targets *S. aureus* to be more efficacious than bleach. We consider this effect size, a reduction in corticosteroid use of more than 1 day a week over 12 weeks, as clinically relevant because of the (low) risk of side effects and a general reluctance of patients to use corticosteroids, resulting in poor compliance and a lack of treatment efficacy [37, 38].

No consensus has been reached yet on a standardized outcome for long-term AD control, the primary goal of our study. The Harmonising Outcome Measures for Eczema (HOME) initiative reached consensus on the use of EASI and POEM as doctor-based and patient-based measures of AD severity, both of which are included as secondary outcomes in this trial [39]. According to the authors of HOME, measures of long-term control could include time to flare and the use of rescue medicine [39]. Next to corticosteroid use, both these study outcomes were included in this study as secondary parameters.

In conclusion, this study will evaluate the effects of 3-month targeted anti-staphylococcal therapy with Staphefekt in moderate to severe AD. The lack of resistance induction allows long-term treatment with this anti-staphylococcal agent. This study will provide the first data on the use of anti-staphylococcal therapy with Staphefekt in AD and may provide new insights into the role of *S. aureus* in the pathophysiology of AD.

### Trial status

The first patient was included in the study in July 2016. Patient recruitment is currently ongoing and the recruitment is expected to be completed by August 2017.

## Abbreviations

AD: Atopic dermatitis
EASI: Eczema Area and Severity index
IGA: Investigator’s global assessment
kDa: KiloDalton
MAAS trial: Microbiome in atopic dermatitis during anti-staphylococcal therapy and the effect on steroid use trial
POEM: Patient Orientated Eczema Measure
Pruritus NRS: Pruritus Numerical Rating Scale
QoL: Quality of life
*S. aureus*: *Staphylococcus aureus*
SPIRIT: Standard Protocol Items: Recommendations for Interventional Trials
